## 2. Method

### 2.1. Design

This quasi-experimental study of healthcare workers and healthcare consumers is a feasibility and pilot study to form the basis for a future, prospective cluster randomised trial (CRT). The single centre study will be conducted at one tertiary hospital in New Zealand. To minimise harm to participants, the key characteristics that will guide the ward selection are stable workforce, predictable patient population, and stable leadership. Based on local conditions, the Chief Nursing Officer will identify and select two wards (intervention and control ward) that meet these criteria. Although everyone on the wards will be invited to participate in the study, it is reasonable to expect that not everyone would want to be enrolled in the research. Thus, the wards are the study setting, and the groups are the enrolled participants on the wards.

Participants will be pre-allocated into four groups. Based on the participants’ location in the hospital, they will be either part of the intervention or the control group. Based on the participants’ position in the healthcare system, they will be either part of the HW group or the HC group. Participants in the HW groups will be constant during the study, while participants in the HC groups will differ across time points. HWs in the intervention ward/group will receive an 8-week immersive empathy education programme and the control ward/group will operate as usual during the research study. HCs will receive care, support and will interact with healthcare workers as usual in both wards/groups. HCs in the intervention ward/group will not be directly affected by the intervention; however, they will experience limited exposure to the education programme (e.g., seeing educational materials on the ward walls).

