The study duration is expected to be approximately 30 weeks (see Figure 1 for the outline timetable for participants). The study will begin with a 3-week recruitment and consenting period prior to delivering the intervention. Baseline assessment of all participants will be continuous in this 3-week period (Weeks 1–3). This is followed by the 8-week intervention. The research team will deliver the immersion programme in the intervention ward, while the control ward will continue to operate as usual with no interaction/engagement during this time with the research team (Weeks 4–12). After delivering the intervention, all participants will complete the second assessment (Week 13–15). HWs in the intervention ward will be invited to participate in focus group interviews about their experiences of the EmpEd (initiation, Week 13; interviews, Weeks 16–17). Three months later, a final follow-up assessment of all participants will complete the quasi-experiment (Weeks 27–30). The design is adaptive in that the study duration and the intervention can be changed if participation and feedback from study participants indicate necessary adjustments for successful study continuation.

An advisory group will be established, and will be made up of health care professionals, healthcare consumer representatives, cultural advisors, and international experts in empathy education. The purpose of the advisory group is to ensure that relevant perspectives and voices are heard and considered in the design of the intervention and the assessment of the EmpEd (e.g., considering different value orientations in a multicultural environment, the work schedule of HW participants, and access to resources). Three advisory meetings will be held over the course of the programme, and a 100 NZD gift voucher per meeting will be offered to each advisor for their contribution.

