### 2.2. Participants

A convenience sample of HW and HC participants will be recruited to complete the study. Participants must provide written, informed consent before any study procedures occur. Eligibility criteria will differ across groups.

HW participants will consist of both registered and non-registered staff, including pharmacists, physiotherapists, occupational therapists, social workers, nurses, doctors, health care assistants, ward clerks, and domestic services staff. With an estimated drop-out rate of 25%, we will recruit up to 138 healthcare worker participants to ensure completion of 110 (55 per ward). Inclusion criteria for healthcare worker participants include (a) being employed in the clinical sites and (b) giving informed consent. Exclusion criteria include (a) working across both the intervention and control wards; (b) agency staff working across multiple wards; or (c) being a medical student, a nursing student, or an allied health student.

HC participants will consist of hospitalised patients and their visiting support persons. With an expected non-completion rate of 10%, we will recruit up to 165 participants to ensure completion of 150 (75 per ward with 25 per timepoint) to complete the study. Inclusion criteria for healthcare consumer participants include (a) ability to understand, read and write English; (b) capacity to give informed consent; (c) (for patients only) being ready for discharge—this is to allow patients to reflect on their experiences and interactions in a non-acute phase of their illness; and (d) (for support persons only) have been actively supporting the patient during their admission (i.e., visited patient at least once per week). Exclusion criteria include (a) being unable to give informed consent; (b) being under the age of 18 years; (c) (for patients only) not predicted to be discharged from the ward between the data collection periods; and (d) (for support persons only) have not been involved in regular support of the patient (i.e., visited less than once a week).

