### 2.3. Procedure

*Recruitment*. To recruit healthcare worker participants, the research team will schedule face-to-face research presentations to nurses and medical professionals on their usual in-service education days. Posters will be placed in the ward areas and research team members will offer information on a one-to-one basis. The nurse managers will also be asked to send out advertisements to their team. Potential participants will be given the participant information sheet and invited to contact a member of the research team if still interested in participating. After the delivery of the intervention, healthcare worker participants from the intervention group will be invited to participate in focus group interviews via email from the research team and verbal invitations from nurse managers. To recruit healthcare consumer participants, advertisements on physical notice boards and table displays will be placed in ward areas. The research team will be present on the wards and invite healthcare consumers on a face-to-face basis to complete the surveys.

*Data collection.* Over the course of the study, quantitative and qualitative data will be gathered at different time points to collect a wide range and type of information for the feasibility and efficacy assessment of the EmpEd. First, surveys will be administered at three time points using Qualtrics software. Each HW participant will be given the survey links via email and will use a unique identifier code, chosen by them, to enter the survey at the commencement of each data collection time point. HC participants will be given a hardcopy to complete with optional assistance provided. Second, two focus groups with approximately 5–10 HW participants from the intervention group will be facilitated after the delivery of the intervention. A research team member, who will not partake in the delivery of the intervention, will organise and facilitate these focus groups to collect qualitative data about the quality and delivery of the programme from the participants’ perspective. The focus group interviews will be transcribed and analysed along with other qualitative data. Finally, during the intervention HW participants will be able to provide hard-copy written feedback about the weekly content of the EmpEd. Participants who discontinue or deviate from the protocol will be excluded from any analysis.

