*Ward Activities.* The ward will be ‘branded’ with a weekly focus corresponding to the weekly topic of the Aroha Passport. A dedicated staff quiet space for healthcare workers, known as the *Empathy Station*, will be located on the ward. In this space of respite, HW participants will be given a white board activity to reflect on the weekly Māori whakataukī (proverb). These activities include prompts as “What are you going to do this week to take care of yourself?” or “Write a kind word to your patients.” The research team will have an active presence at the empathy station to answer questions and accompany visiting healthcare workers. To demonstrate and role model empathy, a twice daily *hydration station* will be part of the education package. Research team members will walk around with a refreshment trolley, offering different herbal/fruit teas, cold water and occasionally fruits, biscuits, and home baking to working healthcare staff. All other times, the trolley will be located in the empathy station where night staff can access the refreshments. During weekdays, team members will also facilitate a daily 5-min *mindfulness* practice in a designated room with dimmed lighting. These sessions will be either guided by a team member or played from different mindfulness mobile apps to provide a wide variety of experiences to the healthcare staff.

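### The team that delivers the programme also invites the patients and visitors who rate empathy, from a convenience sample and with an unnamed helper for the forms; the safeguard set for the focus groups is not stated for these ratings.

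*Protocol article*

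**What the plan says.** All references are to the Protocol article.

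- **Delivery.** Section 2.1: "The research team will deliver the immersion programme in the intervention ward". Section 2.4 adds the visible parts, among them the trolley rounds: "Research team members will walk around with a refreshment trolley".
- **Control ward.** In Weeks 4–12, section 2.1 says "the control ward will continue to operate as usual with no interaction/engagement during this time with the research team".
- **Invitation of raters.** Section 2.3 (Recruitment): "The research team will be present on the wards and invite healthcare consumers on a face-to-face basis to complete the surveys". Notice-board advertisements and table displays are used as well.
- **Sampling.** Section 2.2: "A convenience sample of HW and HC participants will be recruited to complete the study". Section 2.1 adds that "participants in the HC groups will differ across time points".
- **Form completion.** Section 2.3 (Data collection): "HC participants will be given a hardcopy to complete with optional assistance provided". The helper is not identified.
- **Focus groups.** The same paragraph of section 2.3 says "A research team member, who will not partake in the delivery of the intervention, will organise and facilitate these focus groups".
- **Measures.** In section 3.2 the worker scales (ISEI, EOSS, ProQOL) are self-completed. Patients and visitors complete CARE, which rates relational empathy, and AHPEQS, which rates experience of treatment and care.
- **Status.** The HC measures are secondary efficacy outcomes (section 3.2), and section 3.3 treats this part as exploratory, with about 25 raters per ward per time point expected.

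**The concern.** The plan recognises, for the focus groups, that people who deliver a programme should not collect opinions about it. It states no such rule for the ratings that are compared between wards. There, the team with an interest in the result knows which ward was treated and chooses whom to approach, with no rule limiting that choice. Someone unnamed may then help the respondent fill in the form while the respondent is still on the ward.

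Two features make this matter more than usual. First, every worker outcome is a self-report by staff who know whether they took part, so CARE is the only quantitative check on empathy from outside that group. Second, the raters are different people each time. No within-person baseline exists, so a change in the kind of person approached after the programme looks exactly like a change in care. The pilot is meant to inform a cluster randomised trial, and a distorted HC signal could be carried into its design.

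**Working it through.** The point is about conduct, so most of the check sets the statements side by side. The arithmetic only shows how sensitive a small comparison is.

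**1. Who does what**

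| Task | Who, according to the article | Separated from delivery? |
|---|---|---|
| Programme delivery | Research team (2.1, 2.4) | – |
| Focus groups | A member not involved in delivery (2.3) | Yes |
| Inviting HC raters | Research team (2.3) | Not stated |
| Helping with HC forms | Not named (2.3) | Not stated |

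The focus-group rule shows that at least one team member does not deliver the programme. Nothing assigns that member to the HC surveys. If ward staff are the helpers, the people being rated are assisting the rater, so leaving the helper open does not remove the problem.

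**2. What can differ between wards**

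Let the bias on a ward be the effect of selective approach plus (share of forms assisted × uplift per assisted form). The ward comparison is distorted only by the difference:

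net bias = bias(intervention ward) − bias(control ward)

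The invitation and form procedures are described in the same words for both wards, so equal courtesy effects cancel. What need not cancel is the unmasked choice of whom to approach or help, made after the team has spent the programme weeks on one ward only. Comparison with baseline does not remove this, because the asymmetry arises after baseline and the baseline raters are other people.

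**3. The plan's own HC figure**

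Section 3.3 gives a confidence limit of ±0.139 for a proportion of 0.5 with n = 50. The Wald half-width is 1.96 × √(0.5 × 0.5 / 50) = 0.1386, so the figure reproduces. At the expected n = 25 it is 1.96 × √(0.25 / 25) = 0.196. The present point does not depend on either number.

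**4. Sensitivity of a 25-versus-25 comparison**

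Assumptions: no true effect, a net bias of b SD, a two-sided 0.05 test and a normal approximation. The plan intends non-parametric tests, so this is indicative only. The standard error of the difference is √(2/25) = 0.283 SD, and

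P(significant) = Φ(b/0.283 − 1.96) + Φ(−b/0.283 − 1.96)

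| Assumed net bias b (SD) | b / 0.283 | P(significant) |
|---|---|---|
| 0 | 0 | 5% |
| 0.1 | 0.35 | 6% |
| 0.2 | 0.71 | 11% |
| 0.3 | 1.06 | 19% |
| 0.5 | 1.77 | 42% |

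The values of b are scenarios. The article gives no information on the size of b, nor on its sign.

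**The case against.** The strongest defence has five parts.

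- **Shared procedure.** The surveys run the same way on both wards, and the no-contact rule covers only Weeks 4–12. Courtesy towards a researcher therefore arises on both wards and partly cancels. This stands. A reader might infer inflation on the intervention ward alone; the document does not support that.
- **Little contact between raters and deliverers.** A reader might suppose that raters are swayed by a helper they know from the programme. The trolley and quiet room serve staff, section 2.1 describes limited HC exposure, and the follow-up surveys fall in Weeks 13–15 and 27–30, after delivery. That route is open at most to people whose stay or visits reached back into the programme. This stands too, but selective approach does not depend on it.
- **The helper is unknown.** A reader might take it that the delivery team assists with the forms. The sentence does not say so.
- **No size can be derived.** Suppose 20% to 60% of forms are assisted, with an uplift of 0.3 to 0.5 points. The ward mean would shift by 0.2 × 0.3 = 0.06 to 0.6 × 0.5 = 0.30 points, or 0.075 to 0.375 SD at an SD of 0.8. All these inputs are assumed, and the sum also sets the control-ward uplift to zero, which the common procedure contradicts. It should not be read as an estimate.
- **Limited consequence and condensed text.** Feasibility is primary and the HC part exploratory. With one selected ward per arm and no randomisation, a ward difference could not be firmly attributed to the programme even with perfect data collection. Survey staffing may also be set out in a fuller protocol.

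These points lower the weight of the concern. They do not remove it: the article itself fixes convenience sampling and invitation by the research team, and it states the safeguard for one data source and not for the other.

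**Conclusion.** The concern holds in a limited form. The team that delivers the programme invites the raters, without a stated approach rule or masking, and an unnamed person may help with the form. CARE is the only quantitative empathy rating from outside the workforce. Because raters are new at each time point, selective approach or help after the programme cannot be told apart from a change in care.

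The size and direction of any distortion are unknown. The false-positive rates of 6% to 42% depend entirely on assumed net biases of 0.1 to 0.5 SD with 25 raters per ward. Only the part of the bias that differs between wards counts, and the HC results are exploratory in a non-randomised comparison of two wards. A reader might conclude that this flaw alone is what prevents attribution to the programme; the design already limits attribution, and this adds an avoidable source of bias. It also concerns CARE more than AHPEQS, which does not measure empathy as such. It is worth correcting because the correction is cheap.

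**What to change.** Apply the following identically on both wards and at all three time points:

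1. Replace the open convenience approach by consecutive approach of eligible discharge-ready patients, and of their eligible support persons when present, until the target is reached. Keep a log of those approached, declined and completed.
2. Have forms returned sealed.
3. Record on the form whether help was given and by whom. Show the results with and without assisted forms.
4. Do not let ward staff help with the forms.
5. Use existing team members who do not deliver the programme for invitation and help where available. The article identifies only one such member, for the focus groups, so an absolute rule across two wards and three multi-week survey windows might need extra staff.

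**Cost:** less flexible staffing of the survey windows, possibly slower HC recruitment, and a small amount of extra logging, plus envelopes or a return box and one added item on the form.

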### 1.2. Objectives

The primary objective of this pilot study is to evaluate the feasibility of the developed immersive Empathy Education Programme in the clinical setting. First, feasibility will be determined by assessing HWs’ acceptance of the intervention. Acceptability will be measured by five indicators: recruitment rates; completion rates; drop-out rates, HW participants’ written feedback; and their oral evaluation of the programme. Second, feasibility will be evaluated by estimating the programme costs and organisational resources needed to facilitate an EmpEd in the future including time commitment, material and financial resources required to run the programme. The secondary objective is to assess the efficacy of the proposed EmpEd. This secondary objective is dependent on the outcome of the feasibility assessment. That is, if the delivered EmpEd’s acceptance level enables us to collect data and ensure acceptable power for statistical analysis, then we will assess HWs’ level of empathy, subjective wellbeing, organisational satisfaction, and HCs’ satisfaction over time.

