## 3. Measures and Outcomes

### 3.1. Feasibility Outcomes

The feasibility of a prospective CRT on enhancing empathy in the clinical setting will be estimated based on the acceptability of the intervention (1) and the estimated organisational resources needed to continue the programme (2). First, the acceptability of the intervention will be assessed both quantitatively and qualitatively: (a) analysing recruitment, completion, and drop-out rates; (b) monitoring active and passive participation in the intervention; (c) optional weekly written feedback from healthcare worker participants; (d) surveying healthcare worker participants about their prior expectations of the intervention and whether their expectations were met after the intervention; (e) and focus group interviews with approximately 5–10 healthcare worker participants. The main objective of the focus groups is to review and evaluate the EmpEd from the participants’ perspective: evaluation of quality and mode of delivery, usefulness, staff engagement, and specific components of the intervention. Second, to determine the resources needed by the organisation to run an EmpEd, the following need to be considered and estimated: (a) scientific personnel for EmpEd training and supervision; (b) clinical networks and cooperation; and (c) equipment and material costs. Importantly, the EmpEd programme review is not only to measure the feasibility, engagement, and applicability of the programme, but also to assess the viability of continuing aspects of the immersion programme, for example, regular mindfulness sessions or the hydration station.

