### 3.4. Data Management and Analysis Plan

*Qualitative analysis.* Thematic analysis will be conducted on the feasibility of the EmpEd. The analytic interest is on how the experiences of participants are located within the wider socio-cultural context of the ward, which makes thematic analysis a suitable method for our purpose [34]. Thematic analysis will identify themes addressing feasibility issues, for instance, the usefulness of the programme, staff engagement and sustainability. Interview recordings and observational notes will be transcribed. To ensure consistency and accuracy of the analysis, two members of the research team will jointly analyse the data. The thematic analysis will follow Braun and Clarke’s [35] approach and will be completed by using NVivo 12.

The confidence in the quality of the qualitative data, analysis and interpretation will be assured by following the principles of trustworthiness in qualitative research [36]. Trustworthiness will be achieved by ensuring that multiple researchers have oversight of the data collection and analysis process. To ensure credibility of the data, only HWs who have participated in the EmpEd will be recruited into the focus groups, and verbatim quotes from these participants will be used to support themes/subthemes. The use of NVivo 12 to code the data will enhance opportunities for all researchers to evaluate the process of theme development, and it will also facilitate reflection on the analysis process.

*Quantitative analysis.* Descriptive and inferential statistical analysis will be conducted to assess the feasibility and potential efficacy of the EmpEd. Online responses will be registered through Qualtrics. Hard copy survey responses will be manually entered and error checked by looking at ranges and correlations. A minimum response rate of approximately 75% will be used as a cut-off point for the analysis (i.e., lack of completion of the empathy measures). Descriptive statistics will be summarised by using a number of observations, mean, and standard deviation for continuous data, and frequency and percentage for categorical data. To explore efficacy outcomes, nonparametric analyses will be conducted across time points and between groups due to the potential of a small sample size. Missing data will be reported as missing. All statistical analyses will be performed using R Statistical software.

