The secondary aim of the project is to assess the efficacy of the empathy education programme. This is evidently dependent on the feasibility outcome of the study. If the study provides evidence for its feasibility and acceptability, we may expect that our efficacy findings will generate new knowledge regarding the importance of empathetic healthcare environments for patients and support persons and for those working within the New Zealand health care context. It is anticipated that our findings will highlight the importance of empathy in healthcare and the impact of empathy education on healthcare workers and healthcare consumers in the clinical setting.

The current study has practical implications on how to develop an appropriate research design and foster empathetic workforces to improve the quality of patient care and healthcare workers’ wellbeing. First, assessing the feasibility and efficacy of this pilot study provides essential preliminary insights into the challenges of a future CRT and to develop strategies to successfully implement the programme. For example, understanding what drives motivation and drop-out among HW participants can be used to improve the research design of a CRT. Second, our results will provide practical knowledge and information about the reality of planning and delivering empathy education programmes in healthcare contexts that education providers can use for appropriate curriculum design. The empathy immersion programme, when successful, has the potential to be implemented across all District Health Boards in New Zealand and be adapted for other institutions and organisations who are interested in developing empathetic workforces. Future work is planned to assess the feasibility of the empathy immersion programme across different health care settings. Finally, the insights from healthcare consumers about their satisfaction with healthcare services can contribute to patient safety and lead to a better understanding of healthcare consumers needs, which is in line with the current national efforts to measure patient experience [33].

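### Excluding everyone who discontinues or deviates from any analysis contradicts the primary feasibility outcome and leaves efficacy to completers and compliers only

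*Protocol article*

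**What the plan says.** The rule closes the data collection paragraph of section 2.3 (Procedure) in the protocol article: "Participants who discontinue or deviate from the protocol will be excluded from any analysis". That paragraph covers the surveys, the focus groups and the weekly written feedback, and introduces them as serving both the feasibility and the efficacy assessment. Nothing there or elsewhere limits the rule to efficacy.

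The primary outcome is described as follows:

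- Section 1.2 (Objectives): "Acceptability will be measured by five indicators: recruitment rates; completion rates; drop-out rates", followed by the written and oral feedback of healthcare workers (HWs).
- Section 3.1 (Feasibility Outcomes): "analysing recruitment, completion, and drop-out rates", and also "monitoring active and passive participation in the intervention", weekly feedback, and survey questions on whether expectations were met.
- Section 4 (Discussion): "understanding what drives motivation and drop-out among HW participants can be used to improve the research design of a CRT".

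Section 2.2 (Participants) expects 25% of HWs to drop out and sets recruitment at up to 138, to leave 110 completers, 55 on each ward. On efficacy, section 3.4 says that missing data are reported as missing and sets a response cut-off of about 75%. It names no analysis set that would keep the people whom section 2.3 removes.

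**The concern.** A drop-out rate cannot be estimated after the drop-outs have been removed. The rule as written takes out the people whom the primary outcome has to count. It also takes out their written feedback and survey answers, which are the most direct evidence on why the programme did not suit them. The results are meant to shape a later cluster randomised trial, and section 1.2 makes the efficacy assessment depend on acceptance, so a filtered picture of acceptability would carry forward.

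For efficacy, the rule restricts the comparison to those who stayed and complied. Intervention-ward staff have an eight-week programme, including a self-directed booklet to be done in their own time (section 2.4). Control-ward staff work as usual without contact with the research team during that period (section 2.1). Exclusion for departing from the programme can therefore fall on one ward only. Engagement with an empathy programme could plausibly be related to empathy, burnout and satisfaction, which are the efficacy outcomes.

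**Working it through.** **Inputs.** From section 2.2: 138 HWs recruited, 110 completers, 25% drop-out. From section 3.3: 55 per ward and a significance level of 0.05/9 = 0.0056. The documents give no effect size, no SD and no score difference between leavers and stayers.

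**1. The plan's own figure.** 110 × 1.25 = 137.5, which rounds to 138. The recruitment figure is reproduced. (Whether multiplying by 1.25 is the right allowance is a separate matter. At 25% drop-out, 138 leaves 138 × 0.75 = 103.5.)

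**2. Feasibility rates with and without the rule.** Expected drop-outs are 138 × 0.25 = 34.5, that is 34 to 35 people.

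| | All enrolled | Rule applied literally |
|---|---|---|
| Denominator | 138 | 103.5 |
| Completion | 103.5/138 = 75% | 103.5/103.5 = 100% |
| Drop-out | 34.5/138 = 25% | 0/103.5 = 0% |

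The right-hand column is fixed by construction and would be the same at any true drop-out rate. No assumption about outcomes is needed.

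**3. Feedback.** Suppose drop-outs are still counted for the rates. The rule would nevertheless remove from analysis the feedback they wrote before leaving and their answers on expectations. Section 3.1 lists both as acceptability measures, and both bear on the aim in section 4 of learning what drives drop-out.

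**4. Efficacy, illustration only.** If a fraction q of a ward is excluded and those excluded score g SD lower than those kept, the mean of those kept exceeds the mean of the whole ward by q × g. The spurious difference between wards is then

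(q_intervention × g_intervention) − (q_control × g_control).

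Assume g = 0.3 to 0.5 SD on each ward and no programme effect:

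- 25% excluded on both wards: 0.
- 35% on the intervention ward (assumed) and 25% on the control ward: 0.10 × 0.3 = 0.03 to 0.10 × 0.5 = 0.05 SD.
- 25% on the intervention ward and none on the control ward (an extreme case): 0.25 × 0.3 = 0.075 to 0.25 × 0.5 = 0.125 SD.

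A second calculation for the same extreme case assumes a correlation ρ between the outcome and staying, so that the shift is ρ × φ(z_q)/(1 − q). At q = 0.25 this gives 0.042, 0.085, 0.127 and 0.212 SD for ρ = 0.1, 0.2, 0.3 and 0.5. With 69 enrolled per ward and a two-sided normal approximation, the chance of a false positive at 0.0056 becomes 0.007, 0.011, 0.019 and 0.053.

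For scale, 55 per ward with 80% power at two-sided 0.0056 corresponds to a difference of about 0.69 SD on the same approximation.

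**The case against.** The strongest reply is that the authors cannot have meant it. An article that names drop-out rates as an indicator and plans to learn from drop-out will hardly report 0%. The likelier intent is to exclude these people from the analysis of outcome scores. That is a fair guess at intent, but the text does not say so, and on that reading the leavers' feedback and the efficacy set are still affected. A reader might infer that the feasibility result will be biased towards success. The documents support only that it would be if the sentence were followed.

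A reader might also infer that the efficacy exclusions are one-sided, with nearly all control staff kept. The documents do not support this. The 25% in section 2.2 applies to the whole HW sample, the staff reallocation mentioned in section 4 can affect either ward, and control staff can miss surveys. Nor does the article say that an unfinished booklet is a deviation: section 3.1 treats passive participation as something to record, and section 3.4 has deviations logged as incidents. A fuller document may define the term. What stands is that exclusions may be asymmetric.

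The SD figures rest on assumed gaps and assumed exclusion fractions. They vanish if exclusion and gap are equal on both wards, and a stable difference between stayers and leavers would cancel in change scores within the same people. Even the extreme case is small beside 0.69 SD.

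It is also tempting to cite the focus groups, because "only HWs who have participated in the EmpEd will be recruited into the focus groups". But having participated is not the same as having completed, so that sentence does not by itself shut out people who started and stopped.

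Finally, the wards are not randomised, so keeping everyone by ward of enrolment does not remove confounding by ward. That is correct. It avoids adding a second source of selection.

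**Conclusion.** The contradiction between section 2.3 and sections 1.2 and 3.1 is explicit and rests on no assumption. Followed literally at the planned drop-out, the rule removes 34 to 35 of 138 HWs, reports 0% drop-out and 100% completion in place of 25% and 75%, and discards the leavers' feedback. Because it disables named indicators of the primary outcome, the sentence needs to be changed.

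The efficacy part is secondary. The rule imposes a completers-and-compliers comparison whose exclusions may differ between wards and may be related to engagement. The documents fix neither the size nor the direction of any bias, and the SD values above are illustrations, not estimates. The point concerns HWs mainly, because the healthcare consumer samples are different people at each time point.

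**What to change.** Replace the sentence in section 2.3 with three rules:

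1. **Feasibility.** Completion and drop-out rates use all consented HWs as denominator, and the recruitment rate uses all eligible or approached HWs. All feedback and survey answers collected are kept, including those from people who later leave.
2. **Main efficacy analysis.** All consented HWs are analysed by ward of enrolment with every available survey, whatever their participation in the programme. Those who stop the programme but have not withdrawn consent are still sent the later surveys.
3. **Sensitivity analysis.** A completers-only analysis is reported and labelled as such, with what counts as a deviation defined before the data are examined.

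The cost is protocol wording and a few more survey emails, since HW surveys already go out by email. The estimated effect may be slightly smaller. The change cannot recover surveys that are never returned. It helps only where people who stopped or deviated have given, or will still give, data, and the documents do not say how many that would be.
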